#### Physical fitness tests (in-person)

The order of the in-person physical fitness tests is standardized. First, we assess balance and functional mobility and subsequently, functional and maximal muscle strength, aerobic capacity and maximum short exercise capacity (Table 3). All tests are performed according to standardized protocols. These protocols can be found in *Additional file 3*.

#### Physical fitness tests (live-remote)

The live-remote testing sessions are performed via Zoom. Prior to conducting the physical assessments, the researcher checks whether the participant’s testing environment is suitable and safe to conduct the tests. In addition, safety measures (i.e., recording participant’s address and emergency contact details) are discussed with the participant. The live-remote testing sessions are recorded to verify the correct execution of the tests after the sessions. For the different tests, the researcher instructs the participant to change the positioning of the camera to ensure an optimal view.

At the start of the live-remote testing sessions, the participant’s heart rate is measured using the activity tracker. The order of the tests is standardized. First, we assess balance and functional mobility and subsequently, muscle strength and aerobic capacity. All tests that overlap with the in-person setting (i.e., single leg stance, Timed Up and Go test, 30 s sit-to-stand, and Chester Step Test) are conducted according to the same standard operating procedures, as described in Additional file 3*.*

Additionally, a push-up test and a plank position holding time test is performed during the live-remote testing sessions to assess muscle strength [38, 39]. The positions of these exercise are demonstrated during the in-person visits. For the push-up test, participants are asked to complete as many push-ups on knees as possible, while maintaining proper form. The test is stopped when the participant is fatigued and stops the test or fails to maintain proper form. The number of correctly performed push-ups is recorded.

For the plank position holding time test, participants are asked to hold a static plank position as long as possible. The test is stopped when the participant is fatigued and stops the test or fails to maintain proper form. The time in plank position is recorded.

#### Cost-effectiveness

A cost-effectiveness analysis (CEA) will be conducted alongside the trial by comparing the costs and effects of the intervention. The EQ-5D-5L is used to assess effects on health across five dimensions: mobility, self-care, usual activities, pain/discomfort, and anxiety/depression, each rated on five levels of severity [40]. This questionnaire is used to calculate quality-adjusted life years (QALYs). The analysis will be conducted from a societal perspective, including healthcare costs, patient and family costs, and productivity costs. Costs of the live-remote exercise program will be calculated bottom-up. Other direct costs are collected through questionnaires. A healthcare use questionnaire is used, which is based on the iMTA Medical Cost Questionnaire (iMCQ), including cost categories relevant to cancer survivors. Productivity losses are assessed using the modified Productivity Cost Questionnaire (iPCQ) [41].

#### Adherence

Adherence incorporates both attendance to the live-remote exercise sessions and compliance with the exercise prescription according to protocol. For each scheduled session, the exercise professional documents attendance in a case report form and records reasons for missed training sessions. An app (Castor Connect App) is used to capture compliance with all parts of the exercise program. Study participants record all exercise specifications (i.e., number of repetitions/rounds and, if applicable the weight or resistance band used, per exercise) and, if applicable, reasons for deviations from the protocol in the app. If participants prefer, they can also register compliance data on a paper form, in which case the data is entered into the app by the exercise trainer or study team.

#### Satisfaction

At 12 weeks (intervention group) and 24 weeks (wait list control group), we assess satisfaction with the live-remote exercise program, the exercise professionals, the activity tracker, educational resources and supporting exercise app by means of a study-specific questionnaire. In addition, participants who have completed the intervention are invited to provide more in-depth input on how the interaction between participants and the interaction between the exercise professional and participants could be optimized. This is done through a concept mapping approach. Participants can share their insights by either responding to two focus prompts, or by sorting and ranking the responses of others to these focus prompts. Responses are collected through the GroupWisdom application (Ithaca, NY, USA).

#### Sensor-based outcomes

The sensor-based sub-study will assess the feasibility, usability, and subjective experience with the technology and sensor-based exercise guidance, alongside adherence and technological reliability. In this context, usability and the experience of participants and exercise professionals regarding the technology use and sensor-based guidance are assessed using the System Usability Scale (SUS) and semi-structured interviews. Adherence is evaluated based on participant compliance with wearing the sensors (i.e., number of times sensors were worn during and after sessions). Additionally, adherence to the exercise prescription is analyzed, including the time spent within the prescribed heart rate zone (65–75%) during aerobic exercise, and the number of repetitions during resistance exercise. Technological feasibility is assessed through indicators such as device failures, connection errors, and problems documented by participants and exercise professionals.

#### Safety

All (serious) adverse events ((S)AE) are recorded according to the Exercise Harms Reporting Method (ExHaRM) [42]. First, (S)AEs are *monitored and identified* as follows: (1) Participants in both groups are asked by the study personnel about (S)AEs in a standardized manner during all follow-up visits; (2) Participants are asked by their exercise professional, before and after each live-remote exercise session, whether any (S)AEs occurred during or since the last exercise session; (3) Exercise professionals may observe a (S)AE during the exercise program; (4) (S)AE is spontaneously reported by participant between follow-up visits. Second, all (S)AEs, whether or not related to the study, are *assessed and recorded* by the exercise professional. The exercise professional indicates whether or not each event is related to the study. If unrelated, the adverse event is simply noted. If related, a detailed adverse event form is completed, including questions about the setting where the event occurred, its severity and actions taken (e.g., discontinuation or modification of intervention). Third, all (S)AEs are *reviewed* by an internal review board for relatedness to the exercise program or to the study measurements. All adverse events are coded using the Medical Dictionary for Regulatory Activities (MedDRA) to ensure standardized classification and grouping of similar events. SAEs are reported to the accredited ethical committee that approved the protocol, according to the requirements of that ethical committee.

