### Study outcomes

Participants visit the study center for assessments at baseline, 12 weeks, and 24 weeks (wait list control group only), with 12 weeks being the primary time point. Patient-reported outcomes are assessed using online questionnaires, which participants either receive via Castor EDC shortly prior to the study center visit or complete during their visit, prior to the physical tests. Patient-reported outcomes are also assessed remotely at 6 weeks, 18 weeks (wait list control group only), 24 weeks (intervention group only), and 36 weeks. Additionally, participants receive phone calls at these time points to collect information on potential (serious) adverse events ((S)AEs), changes in medication, and health status (e.g., cancer recurrence). During the in-person visits, anthropometrics and physical fitness/performance are assessed and blood samples are drawn. To inform whether the intervention could be delivered entirely live-remote in routine clinical practice, we assess if live-remote testing is also feasible. Therefore, we perform live-remote physical fitness and function testing in all wait list control participants at 12 and 24 weeks as well.

Socio-demographic data are assessed at baseline with a study-specific questionnaire. Medical data are based on patient-report or retrieved from medical records. Personal data are coded and all data are handled in compliance with the General Data Protection Regulation (GDPR) (EU) 2016/679. Validity of the data is checked by an independent monitor.

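### To week 12, adverse events are sought at every session in the exercise arm but only at weeks 6 and 12 in controls, and detailed recording is described only for events first called related

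*Protocol article*

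**What the plan says.** The Safety section of the protocol article lists four ways of identifying events.

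- Both arms: "Participants in both groups are asked by the study personnel about (S)AEs in a standardized manner during all follow-up visits".
- Session questioning: "Participants are asked by their exercise professional, before and after each live-remote exercise session".
- Session observation: "Exercise professionals may observe a (S)AE during the exercise program".
- Spontaneous reports between visits, open to either arm.

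The Study outcomes section adds remote contacts at week 6 and at later time points: "participants receive phone calls at these time points to collect information on potential (serious) adverse events". Week 12 is an in-person visit for both arms. The Wait list control group section starts the controls' exercise program only after the 12-week assessment.

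On recording, the Safety section gives assessment of all events, related or not, to the exercise professional: "The exercise professional indicates whether or not each event is related to the study". A related event gets a detailed form covering setting, severity and actions taken. Otherwise, "If unrelated, the adverse event is simply noted". An internal board then reviews all events for relatedness to the program or to the study measurements. All events are MedDRA coded, and SAEs are reported to the ethics committee.

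**The concern.** There are two separate problems.

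The first is ascertainment. During the randomized 12 weeks, two of the four detection routes exist in one arm only. A table of event counts by arm over that period would show the effect of exercise and the effect of asking more often, with no way to separate them. The Introduction names safety among the things that adequately powered studies still have to establish for live-remote exercise, so readers are likely to look at such a table.

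The second is recording. The amount of detail kept depends on a first relatedness call by the person who delivers the intervention and knows the allocation. Before week 12 controls have no exercise professional, so it is unclear who makes this call for them. Few of their events could be called related anyway, apart from those tied to study measurements. If the rule is followed as written, severity would be recorded routinely for some exercise-arm events and rarely for control events. Detail not taken when the event is reported may be hard to recover at analysis.

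**Working it through.** The article states no figure on this point, so there is none to reproduce. The check counts the scheduled enquiries and then follows one event through the recording rule.

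**Inputs**
- Sessions: 3 per week for 12 weeks (Live-remote exercise program).
- Enquiries per session: 2, before and after (Safety).
- Contacts common to both arms up to week 12: 2, the week-6 call and the week-12 visit (Study outcomes). I assume the week-6 call uses the same standardized question as the visits.
- Control sessions before week 12: 0 (Wait list control group).

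**Enquiries from baseline to week 12**
- Sessions = 3 × 12 = 36.
- Intervention enquiries = 36 × 2 + 2 = 74. Control enquiries = 2. Ratio 37 to 1.
- Counting the before and after questions of one session as a single occasion: 36 + 2 = 38 against 2, or 19 to 1.

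The article gives no attendance figure. Under assumed attendance:

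| Attendance (assumed) | Sessions | Enquiries, intervention v control | Occasions, intervention v control |
|---|---|---|---|
| 100% | 36 | 74 v 2 | 38 v 2 |
| 80% | 29 | 60 v 2 | 31 v 2 |
| 60% | 22 | 46 v 2 | 24 v 2 |

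The imbalance stays large at any plausible attendance.

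**What this could do to a rate comparison (illustration only)**

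If both arms have the same true event rate, the apparent rate ratio equals capture in the intervention arm divided by capture in controls. The article gives no capture probabilities. With assumed capture of 80–100% in the intervention arm and 30–70% in controls:
- lowest: 0.8 / 0.7 = 1.14
- middle: 0.9 / 0.5 = 1.8
- highest: 1.0 / 0.3 = 3.33

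The width of this range shows that the size cannot be estimated from the article.

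**Following one event through the recording rule**
1. The event is identified by any of the four routes.
2. The exercise professional makes the first relatedness call. The Recruitment and randomization section says the study team cannot be blinded.
3. If related, setting, severity and actions taken go on a form. If unrelated, the event is noted, and the article does not say what the note contains.
4. The board reviews relatedness for all events. Nothing says that the form is completed when the board reverses an unrelated call.

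For a control event before week 12, step 2 has no obvious person to carry it out, and step 3 will nearly always end in the note.

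Table 3 adds a further inconsistency. It lists only events related to exercise, whereas the Safety section covers all events whether related or not. The two should be reconciled.

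**The case against.** The strongest reply is that no between-arm test, rate ratio or table of adverse events is announced under Statistical analysis. Asking at every remotely supervised home session is proper surveillance of exercise harms, and it cannot be matched in people who have no sessions. The article also already has a common basis for comparison in the standardized questions put to both arms. Table layout and source coding belong in the case report form and the analysis plan, which are not shown.

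Much of this stands. Session monitoring is appropriate and should not be reduced, and no stated test is biased. Analysis detail absent from a condensed article is no fault. What remains is a data-collection rule that the article states outright: detail depends on the first relatedness call. That rule acts before any analysis plan does.

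A reader might also infer stronger points that the text does not support.

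- *A harm wrongly called unrelated can never be found.* The board reviews all events, all are MedDRA coded, and Table 3 names medical records as a source. The gap is the missing step for completing the detail.
- *Severity cannot be compared between arms at all.* The content of the note is not described, serious events are distinguished from others, and SAEs go to the ethics committee, so some detail may exist elsewhere.
- *Controls are covered only by the two contacts.* That is true of active questioning, but spontaneous reports are open to them too.
- *Exercise will look less safe.* More frequent asking would tend to raise counts in the exercise arm, but an unblinded deliverer inclined to call events unrelated would lower the related counts. The net direction is uncertain.
- *A specific inflated rate ratio.* Any such figure rests on assumed capture rates.

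**Conclusion.** The point holds in limited form. To week 12 the arms differ in active enquiry by up to 38 occasions to 2, or 74 enquiries to 2, assuming full attendance and counting the week-6 call and week-12 visit as the contacts common to both arms. Event counts by arm over that period would therefore not be comparable as they stand, by an unknown amount. Separately, detailed fields are described only for events that an unblinded exercise professional first calls related. The assessor for control events before week 12 is not clear from the text, and no step completes the detail if the board disagrees.

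The ascertainment problem is confined to the randomized 12 weeks, because controls then receive the program with the same procedures. It bears on the interpretation of safety and leaves the primary efficacy analysis untouched.

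**What to change.** Keep session monitoring as it is, and make these changes.

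1. Add a field giving the source of each event: standardized question, session question, observation or spontaneous report.
2. Base any between-arm comparison to week 12 on events elicited by the common standardized questions at weeks 6 and 12. In the intervention arm, record the answers to those questions in full even when the event was already logged at a session; otherwise the restriction would undercount that arm. Report session-elicited, observed and spontaneous events descriptively.
3. Record severity, seriousness, setting and action taken for every event in both arms before relatedness is judged, at minimum for all SAEs and in-session events. Name study personnel as responsible for this in controls.
4. Analyse the board's relatedness judgement, and keep the exercise professional's call as a recorded first opinion.
5. Align the adverse event row of Table 3 with the Safety section.

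The cost is one case report form field, a longer form for events now only noted, and some wording. The downside is modest extra data entry. A residual limit is that repeated session questioning may sharpen recall at weeks 6 and 12 in the intervention arm, so the restricted comparison reduces the detection difference but may not remove it.

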### Sample size

The sample size is based on the expected minimal improvement of either or both primary outcomes, i.e., HRQoL or the participant’s most burdensome side effect, from baseline to 12 weeks post-baseline relative to wait list control. To adjust for multiple testing, the Bonferroni-Holm method will be used. A Cochrane meta-analysis on RCTs with exercise interventions in breast cancer survivors after adjuvant chemo- and/or radiotherapy reported an effect size (95% CI) of 0.39 (0.21–0.57) for HRQoL and 0.34 (0.05–0.62) for depression, 0.33 (0.18–0.49) for perceived physical function, and 0.32 (0.18–0.47) for fatigue [43]. The subgroup of studies with combined aerobic and resistance exercises showed a higher effect size of 0.63 (0.08–1.19) for HRQoL and 0.47 (0.02–0.92) for fatigue. A meta-analysis comprising patients with mixed cancer entities after end of treatment also showed an effect size of 0.47 (0.29–0.65) for combined exercise on fatigue [44]. Further, higher effects are typically reached in studies enrolling only patients with the targeted symptom or side effect as well as with supervised compared to unsupervised exercise interventions [9, 11]. Hence, our planned intervention is expected to have effects that are in the higher range of previously reported studies. We performed a simulation study to calculate the power of the study considering that two primary outcomes will be tested and that a meta-analytic procedure will be used to obtain an average standardized effect size for participant’s most burdensome side effects. We assumed an effect size of 0.35 to obtain a conservative estimate for the required sample size. In the simulations, we assumed a correlation of 0.3 between the two primary outcomes. In case of a common effect size of 0.35 for HRQoL and participant’s most burdensome side effects in all four strata, a sample size of 280 individuals living beyond primary curative cancer treatment (*n* = 140 per study group) was found to yield 80% power to detect an effect on each individual primary outcome, with an overall alpha of 0.05. To account for a potential drop-out of around 20%, a total number of 352 individuals will be enrolled (*n* = 176 per study group). This sample size will also facilitate exploratory moderator and subgroup analyses to better understand which individuals benefit most from exercise.

#### Statistical analysis

Descriptive statistics will be used to characterize the study population at baseline. Questionnaire scores will be calculated according to published scoring manuals. All analyses will be performed according to the intention-to-treat principle, including all randomized participants in the groups to which they were assigned, irrespective of adherence.

A positive result at the 12-week assessment of any of the two primary outcomes (i.e., HRQoL and the participant’s most burdensome side effect) is of main interest. Statistical testing for the intervention effect will be done separately for each primary outcome. HRQoL will be assessed using the EORTC QLQ-C30 summary score. For the participant’s most burdensome side effect, a meta-analytic procedure will be used to obtain an average standardized effect size (ES) (see below for further details). To adjust for multiple testing, the Bonferroni-Holm method will be used to maintain an overall alpha level of 5%. Two-sided 95% confidence intervals for the effect estimates for both primary outcomes will be presented.

A mixed model for repeated measures will be used to assess the intervention effect on the primary outcome HRQoL, while taking the hierarchical structure of the data into account (participants nested within countries). Models will be adjusted for the baseline value of the outcome and stratification factors (i.e., sex, country and the participant’s most burdensome side effect) and will include participants for whom the outcome is observed at two or more timepoints. Time since completion of curative treatment will be added as a cofactor, if there is an imbalance between groups. The primary contrast will be the comparison of the mean outcomes at 12 weeks between the intervention and control group adjusted for the baseline value.

As the participant’s most burdensome side effect will differ between participants, inference for this primary endpoint in the whole study sample will be based on a pooled estimate of the stratum-specific standardized mean differences. A two-step procedure will be used. First, standardized ES will be calculated in the four strata separately (e.g., for all patients with fatigue as main side effect, an ES will be calculated). Subsequently, these four standardized ES’s will be pooled using a fixed-effect meta-analytic model. This pooled standardized ES can be interpreted as a stratum-size weighted average of the standardized ES for participant’s most burdensome side effect at 12 weeks.

The same analysis as for HRQoL will be performed for secondary outcomes assessed at more than 2 time points. Outcomes assessed at only two time points (i.e., physical fitness and performance) will be analyzed as between-group differences in outcomes using ANCOVA, adjusted for baseline values and stratification factors. All secondary analyses will be considered exploratory with statistical testing being done at the 5% significance level. For all secondary outcomes, ESs and 95% CIs are reported without *p*-values, according to the European Medicines Agency (EMA) guidelines. The statistical analysis plan is included in the IRB study protocol.

To assess whether a similar intervention effect is seen in the whole study sample or whether subgroups can be identified that benefit most from the intervention, potential moderators of the exercise effect will be investigated, e.g., for main side effect groups, sex, cancer type, or baseline fitness level. Further, to explore potential underlying mechanisms (e.g., inflammation) of exercise effects on the primary outcomes, mediation analyses will be performed.

Missing values of the primary outcome variables as well as all other patient-reported outcomes will be assumed to be Missing at Random (MAR) for primary analyses and dealt with using mixed models for repeated measures (HQRL) and multiple imputation (most burdensome side effect). Intercurrent events (e.g., death, cancer recurrence, non-adherence (i.e., < 80% of scheduled sessions due to external reasons), contamination) will be handled according to our study protocol.

